#### Inclusion criteria

Age 18 years or olderDiagnosed with completely excised breast cancer (stage 0–3) or ductal carcinoma in situ (DCIS)Have undergone breast-conserving surgery and are scheduled to undergo adjuvant breast RTAble to provide informed consent (may involve a qualified interpreter for spoken language other than English)Eastern Cooperative Oncology Group (ECOG) performance status 0–2Any infra-mammary skin fold of 0.5 cm or larger and/or palpable lateral breast tissue falling posterior to the mid-axilla line with the breast unsupported in the supine treatment positionAbility to complete skin self-assessments by PRO questionnaire

#### Exclusion criteria

Inability to comply with experimental arm of trialPrevious RT to either breast or chestPlanned boost to infra mammary area (patients undergoing boost RT are otherwise eligible, assuming inclusion criteria are met)Planned partial breast irradiation that does not include the infra-mammary regionUse of Mepitel® or other wound contact layer product while on treatmentFailure to heal surgical wound or significant post-operative wound infectionPresence of significant connective tissue disease (e.g., systemic sclerosis, systemic lupus erythematosus)Known radiation hypersensitivity phenotype (e.g., ataxia, telangiectasia)Inability to complete PRO questionnaire (including skin self-assessments) or to be assessed remotely out to 7 weeks after the start of breast RT

### Interventions

#### Radiation therapy

For both study arms, breast RT protocols currently in use at the treating centres will be used. Dose fractionation schedules include 26 Gy in 5 daily fractions, 42.5 Gy in 16 daily fractions, 40 Gy in 15 daily fractions, 45 Gy in 25 daily fractions, and 50 Gy in 25 or 28 daily fractions. The extended fractionation schedules are generally reserved for patients with a large separation (> 24 cm) or significant post-operative changes. Partial breast treatments are acceptable if the inferior breast skin is included in the treated volume.

The treatment delivery will generally consist of a tangent pair of photon fields with or without internal mammary, supraclavicular, and/or axillary nodal fields. Combinations of 6 MV, 10 MV, 15 MV or 18 MV photons are permitted as required to meet planning dose constraints. Volumetric modulated arc therapy (VMAT) is currently under consideration.

Additional boost radiation to the tumour bed may be prescribed at the discretion of the radiation oncologist. Boost may be delivered using MV photons or electrons before, during, or following breast RT.

In both arms, patients will be planned and treated in the supine position on an angled breast board. In addition, patients must be indexed to the breast board and the breast board must be indexed to the treatment couch. Deep inspiration breath hold (DIBH) for left breast patients may be used to reduce dose to the heart [34] in both study arms. Standard skin care instructions will be utilized.

#### CT simulation

CT simulation will be performed with the patient in supine position for both study arms. The preferred patient position is both arms above the head with elbows resting comfortably on a wing board. Variation in arm position (one arm up) is acceptable if the patient is unable to achieve both arms up. Arm position shall be documented on the treatment planning data sheet. Simulation will be performed using the standard CT protocol at the treating centre, confirmed during the credentialing review. Setup marks will be placed laterally and medially, and tattoos will be applied for future setup at the treatment unit. The preferred method for eliminating patient roll at the time of treatment is to place lateral tattoos on each side of the patient with arms up at the time of simulation. Alternate methods will be confirmed at the time of the credentialing review.

Detailed technical descriptions and figures of CARA are published elsewhere and similar to the completed pilot studies [24–26]. In the experimental arm, CARA settings will be adjusted on a patient-by-patient basis to eliminate the IMF and lateral tissue droop such that that all palpable breast tissue sits anterior to the mid-axilla line. Patient-specific CARA settings will be captured to include in the setup instructions at the treatment unit.

Patients in the control arm will be positioned according to standard practice of care which may include no support, a small foam wedge in the skin fold, a thermoplastic shell, or an alternative supine breast support approved at the time of credentialing review. The method will be recorded with the treatment planning data. No changes to standard practice in the control arm, as reported on the credentialing survey, are permitted during this study without consultation with the steering committee.

#### Target volumes and organs at risk

The breast clinical target volume (CTV) includes the palpable breast tissue and glandular and fatty breast tissue visualized by CT. The planning target volume (PTV) includes a 2 cm beam margin superior and inferior to the CTV and extends to the chest wall-lung interface but does not include skin unless clinically necessary. Supraclavicular, axillary, and internal mammary nodal PTVs will be identified and contoured according to current standard practice at the treating center. Up to 5 surgical clips within the breast PTV will be contoured when available, for positional measurement during imaging at the treatment unit.

An optimization target volume (OTV) is derived during the treatment planning process from a specified isodose surface (typically 30–50% of the prescribed dose) for open fields at the chosen lateral and medial beam angles, including any required blocking, as specified by the radiation oncologist. This isodose contour is cropped 5 mm in from the skin and lung and then labelled as OTV or Breast_Eval. Other approaches to target volume segmentation may be approved at the credentialing review.

The whole body and OARs will be contoured according to RTOG Atlas definitions. OARs include heart, ipsilateral lung, and any other OARs used in standard practice at the treating center. To mitigate difficulties with contouring, the maximum heart dose will serve as a temporary surrogate to the left anterior descending artery (LAD) dose for left breast cases. Future, detailed LAD dose analysis may be performed.

#### Treatment planning and dose constraints

Treatment planning will be performed for both study arms according to current standard of care using the Varian Eclipse AAA algorithm (V13.6) or equivalent, as assessed at credentialing or during the trial if system upgrades occur. Correction for lung inhomogeneity will be used.

PTV, OTV or Breast_Eval coverage by the 95% isodose surface is required. The dose homogeneity objective is V105% < 2% of the OTV. Beam energy may be adjusted as required to achieve PTV coverage and homogeneity criteria, however PTV coverage will take priority over dose homogeneity if the latter cannot be met. For treatments of 15, 16, 25, or 28 fractions, ipsilateral lung V20 Gy shall be ≤ 15% of the lung volume (≤ 35% if regional nodes are treated) and V25 Gy heart shall be ≤ 5% of the heart volume. For 26 Gy in 5 fraction treatments, ipsilateral lung V8 Gy shall be ≤ 15% of the ipsilateral lung volume, heart V1.5 Gy shall be ≤ 30% and heart V7 Gy shall be ≤ 5% of the heart volume. Sliding window or field-in-field (step and shoot) IMRT may be used as available at the treating center.

All treatment plans in this study will be approved by the treating oncologists and designated physicists at each site, including a quality assurance check on all contours. All constraint violations will be noted on the planning data form.

#### Treatment verification

Body and breast position during treatment will be verified with standard of care electronic portal imaging or kV imaging. Additionally, weekly kV CBCT will be performed, when achievable, to monitor the position of segmented surgical clips (when present).

### Data collection

#### Baseline assessment

Data collection activities are shown in Table 1. Patients will have a baseline assessment prior to the first treatment. Patient height and weight, BMI, age, smoking status, RT prescription (including boost), adjuvant chemotherapy, brassiere size (band and cup size), IMF skin fold depth in treatment position, and presence of other skin folds will be recorded. The skin will also be assessed at baseline for any pre-existing conditions such as erythema, telangiectasia, desquamation, or infection. At CT simulation, a baseline photograph of the IMF skin will be acquired as well as a photo of the patient in treatment position. A PRO questionnaire is also collected at baseline.

**Table 1 Tab1:** Schedule of activities and data collection

**Study Activity**	**New patient appointment with radiation oncologist**	**Prior to CT simulation**	**Prior to first treatment**	**Weekly during Breast RT**	**Post-RT weekly to 7 weeks from start of breast RT**
Introduction to study	**X**				
Inclusion/exclusion criteria screening	**X**	**X**			
Informed consent obtained		**X**			
Enrollment and randomization		**X**			
Baseline assessment			**X**		
Patient-reported outcome questionnaire			**X**	**X**	**X**
Skin assessment performed by staff			**X**	**Last week of RT, or for five-day fractionation, last day of RT**	**Optional per patient preference**
Skin dose measurement				**Up to three times per patient; optional for sites other than the coordinating site**	
Timing of clinical flow				**X**	
Standard imaging				**X**	
CBCT imaging				**Up to three times per patient**	
Therapist satisfaction				**Last week of RT, or for five-day fractionation, last day of RT**	

#### Patient-reported outcomes

PRO shall be collected using the POSI methodology [32, 33]. The PRO questionnaire items are summarized above (section *Secondary Endpoints*) [see Additional file 1]. Patients who do not complete the PRO questionnaire on schedule will be contacted by the trial staff to follow-up.

The questionnaire will be available using tablets available in the clinic and by electronic copy post-RT. Alternatively, a physical copy can be delivered to the patient by the trials team, or it can be completed remotely with the assistance of the trials staff if the staff member is blinded to the treatment arm. The PRO questionnaire is currently available in English, Spanish, French, Hindi, Punjabi, and Chinese. Other translations can be made available upon request.

#### Staff skin assessments

Staff radiation therapists, nurses, or radiation oncologists blinded to the treatment arm will perform skin assessments. Staff performing these assessments are required to undergo specific training for this purpose. An in-house MD scoring tool specifically for the IMF will be used in addition to CTCAE V4.0 skin toxicity criteria. Staff skin assessments are required at baseline and during the last week of treatment (or in five-fraction prescriptions, required on the last day of treatment). If the patient is able and willing, staff skin assessments will also be completed weekly thereafter, out to 7 weeks after the start of breast RT.

Each staff skin assessment includes taking photographs of the treated skin in the IMF. Photos of other areas of skin experiencing MD at the time of each assessment may also be acquired. For patients assessed remotely, the patient may be asked to provide photographs of their skin taken at the time of the assessment.

While the method of breast positioning (i.e., Arm 1 or Arm 2) will be open label to the patient and treating staff, it is preferred that staff performing the follow-up skin assessments be blind to which arm of the study participants are in and not have access to the randomization allocation data. If this is not possible (such as in smaller centres), one additional trained study member will perform blinded assessment using photographs taken of the treated IMF area. If there is disagreement between the two assessments, a third trained study member will perform blinded assessment using the photographs. The final assessment of the primary outcome will be by majority vote.

#### *In-vivo* skin dosimetry

GafChromic™ film will be used to monitor skin dose on an around the infra-mammary breast skin during treatment on three fractions for treatment regiments ≥ 15 fractions and on one fraction for 5 fraction treatment regimens. Dose area statistics for area of skin receiving > 50% of the prescribed dose will be reported for each patient at the central coordinating centre, based on the average measured dose distribution for each patient.

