Interpretation of study results with respect to MD is made challenging by the fact that in standard scoring systems, MD appears in both grades 2 and 3 (e.g., Radiation Therapy Oncology Group (RTOG) and National Cancer Institute – Common Terminology Criteria for Adverse Events (NCI CTCAE V5.0)). In addition, many studies do not document BMI or the presence of skin folds, and many studies do not monitor skin toxicity out to two weeks post-treatment when at least 10% of skin reactions peak [8] for standard fractionation schedules, which can result in under-reporting of MD.

In breast RT, skin dose depends on factors including the planning technique, dose constraints, dose prescription, and beam energy. Patients having skin folds during treatment are expected to develop MD in the fold because delivering the prescribed breast dose involves the skin fold dose reaching over 95% of the prescription dose, as it lies within the treatment volume. The risk of MD has also been linked with the volume of the treated breast receiving 105% or more of the prescribed dose (breast V105%) [21–23].

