Having demonstrated the potential clinical benefit of CARA through reduction in doses to organs at risk (OARs) [26], the current study is designed to assess the effectiveness of utilizing CARA V3.0 to reduce the incidence of acute skin reactions in the IMF in patients at high risk of MD undergoing breast RT. In this protocol, the IMF refers to the areas of skin on the inferior breast surface and on the chest that are in contact when the breast is unsupported in the supine position. The IMF is effectively eliminated when using CARA, but skin reactions are being monitored on this skin area after removal of the breast support, post-RT delivery. Compared to the pilot phase II trial, this is a phase III randomized controlled trial (RCT) on a larger population that incorporates improvements from the pilot and the use of PROs for the primary outcome measure. In addition, a discussion of the clinical acceptability of CARA, with respect to workflow measures, setup reproducibility, and therapist satisfaction, will be provided.

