## Methods/Design

### Objectives

The primary objective of this study is to determine whether CARA V3.0 can reduce the incidence of moist desquamation in the IMF for patients with large or pendulous breasts undergoing breast RT in the supine position.

The secondary objectives of the study are as follows:To assess whether the severity of MD in the IMF can be reduced using CARA V3.0.To assess whether overall breast skin reaction scores can be reduced using CARA V3.0.To assess if CARA V3.0 reduces the volume of ipsilateral lung receiving 20 Gy or more (V20Gy).To assess if CARA V3.0 can reduce or maintain the volume of heart receiving 25 Gy or more (V25Gy) for left breast patients.To assess if CARA V3.0 can reduce the volume of body receiving greater than 50% (V50%) and greater than 105% (V105%) of the prescribed dose.To determine a dose-area parameter that is predictive of MD.To compare workflow and breast position reproducibility between the two study arms.To compare the PROs for quality of life measures and comfort during treatment setup between the two study arms.To compare radiation therapist experience between the two study arms.

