#### Statistical methods – secondary outcomes

The eight secondary endpoints will be compared between the two study arms as follows:Degree of MD in the IMF: Peak measured area (cm^2^) of patchy MD and confluent MD will be compared where data is available. It is anticipated that a good proportion of patients will have no MD and hence a measured area of zero. Thus, we will divide the outcome into four categories, the first being zero and the other three will be equal sized groups based on their area score. We will then use the linear trend chi-square test to determine whether the groups differ in their distribution of scores.Peak (worst) modified NCI CTCAE scores for radiation dermatitis will be compared using the chi-square test for trend [36].Dose-volume statistics: values for heart, lung, and body will be compared using the Mann–Whitney U test.Dose-area statistics (*in-vivo* dosimetry): Measured skin dose-area statistics will be compared within both study arms. The measured skin dose-area data for patients developing MD in the location where the dose was measured will be compared with that of patients not developing MD in that location to determine if a dose-area metric predictive of MD can be found for either arm.PRO: The peak (worst) PRO breast symptom scores will be compared using a between-groups t-test, or if data do not conform to test assumptions, the non-parametric Mann–Whitney U test. The requirement for steroid cream and analgesics will be compared using the chi-square test, or Fisher’s exact test, if appropriate.Clinical workflow: Time for patient setup will be compared between study arms using a between groups t-test.Reproducibility of patient setup, as assessed by variation in surgical clip positions measured on imaging will be compared between study arms using the F-test.Therapist satisfaction: Therapist satisfaction with the setup procedure as measured by the questionnaires will be compared using a linear trend chi-squared test.

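### The skin-dose comparison of patients with and without moist desquamation takes no account of fractionation schedule, and the one dose level named, above 50% of prescription, means 13 to 25 Gy depending on schedule

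*Protocol article*

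**What the plan says.** The sixth secondary objective in the protocol article (Objectives) is "To determine a dose-area parameter that is predictive of MD".

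The data come from film on the skin. The section In-vivo skin dosimetry says: "Dose area statistics for area of skin receiving > 50% of the prescribed dose will be reported for each patient", and that this is "based on the average measured dose distribution for each patient". No other skin-dose level is named. Film is exposed on three fractions for courses of at least 15 fractions, and on one fraction for five-fraction courses. Table 1 makes the measurement optional outside the coordinating site. In the control arm film is placed only where this can be achieved (Dose-area statistics measured in-vivo on breast skin).

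Under Statistical methods – secondary outcomes, patients who develop MD where dose was measured are compared with those who do not, "to determine if a dose-area metric predictive of MD can be found for either arm". Fractionation does not appear in that item.

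Under Radiation therapy, "Dose fractionation schedules include 26 Gy in 5 daily fractions" and, at the other end, "50 Gy in 25 or 28 daily fractions", with 40 Gy in 15, 42.5 Gy in 16 and 45 Gy in 25 between them. The same section says the longer courses mostly go to patients with separation above 24 cm or marked post-operative change. Background counts large mid-breast separation among the features of the group at highest MD risk. For skin inside a fold it says "delivering the prescribed breast dose involves the skin fold dose reaching over 95% of the prescription dose".

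**The concern.** Two features of the plan weaken the search for a predictive measure.

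**Schedule.** Patients with MD and patients without it are not randomised groups, so randomisation does not balance schedule between them. A percentage of prescription stands for different absolute doses under different schedules. Schedule is also tied to baseline MD risk through breast separation. If schedules are combined, an apparent dose-area effect may be a schedule or breast-size effect, and a real one may be hidden.

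**Dose level.** The article's reason for expecting MD in a fold is that the skin there receives close to the full dose. A cut-off at half the prescription separates patients poorly if most of the skin under the film already exceeds it.

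At stake is the reading of one secondary objective. A null result could be reported as showing that skin dose-area does not predict MD, and a positive result could be carried into planning as a skin-dose constraint. Neither would be secure.

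**Working it through.** The article gives no figure of its own to reproduce on this point, so the check is direct arithmetic plus a comparison of sections.

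**1. What 50% means under each schedule.** Inputs: the schedules under Radiation therapy. Threshold dose D = 0.5 × prescription; dose per fraction d = D / number of fractions. To allow for fraction size, EQD2 = D × (d + α/β) / (2 + α/β). The article gives no α/β, so 10 Gy and 3 Gy are shown as assumptions.

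| Schedule | D (Gy) | d (Gy) | EQD2, α/β = 10 | EQD2, α/β = 3 |
|---|---|---|---|---|
| 26 Gy / 5 | 13.0 | 2.60 | 13.65 | 14.56 |
| 40 Gy / 15 | 20.0 | 1.33 | 18.89 | 17.33 |
| 42.5 Gy / 16 | 21.25 | 1.33 | 20.06 | 18.39 |
| 45 Gy / 25 | 22.5 | 0.90 | 20.44 | 17.55 |
| 50 Gy / 25 | 25.0 | 1.00 | 22.92 | 20.00 |
| 50 Gy / 28 | 25.0 | 0.89 | 22.69 | 19.46 |

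For example, 13 × (2.6 + 10)/12 = 13.65 and 25 × (1.0 + 10)/12 = 22.92. Highest over lowest:
- nominal dose: 25/13 = 1.9
- EQD2 with α/β = 10: 22.92/13.65 = 1.7
- EQD2 with α/β = 3: 20.00/14.56 = 1.4

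**2. Whether this is peculiar to 50%.** It is not. At 95% of prescription the nominal range is 24.7 to 47.5 Gy, again 1.9-fold. With α/β = 10, EQD2 runs from 24.7 × 14.94/12 = 30.75 to 47.5 × 11.9/12 = 47.10, or 1.5-fold. With α/β = 3 it runs from 24.7 × 7.94/5 = 39.22 to 47.5 × 4.9/5 = 46.55, or 1.2-fold. A higher cut-off alone therefore does not remove the need to handle schedule.

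**3. Whether schedule is linked to MD risk in the article's own terms.** Radiation therapy links the longer schedules to separation above 24 cm, and Background links large separation to MD. Randomization procedure and tracking stratifies by fractionation, and the primary logistic model adjusts for it. Treatment planning and dose constraints sets the lung limit at 20 Gy for 15 to 28 fractions but at 8 Gy for five fractions, so the article already treats dose thresholds as schedule-specific. The dose-area comparison has no counterpart to any of this. Film precision also follows schedule, with one reading for five-fraction courses and three averaged readings for the rest.

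**4. How a lone 50% cut-off might perform in patients with a fold.** This is a simulation on assumed inputs: 150 cm² of film, fold skin at full dose over a depth of 0.5 to 6 cm and a width of 10 cm, and MD risk driven by the area above 95%.

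| Mean skin dose outside the fold (% of prescription) | AUC, area above 50% | AUC, area above 95% | CV of area above 50% |
|---|---|---|---|
| 45 | 0.64 | 0.78 | 0.32 |
| 55 | 0.58 | 0.79 | 0.18 |
| 70 | 0.56 | 0.79 | 0.03 |
| 80 | 0.56 | 0.78 | 0.01 |

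As the surrounding skin dose rises, the area above 50% approaches the whole film and its spread shrinks. The 95% level is favoured by construction, because MD was made to depend on it. The table shows how saturation would act and is not evidence about real patients.

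**The case against.** A reader might infer that a 50% level cannot yield a predictive parameter, so that the objective cannot be met. The text does not support that, for four reasons.

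- The wording can equally mean dose-area statistics within the region above 50%, which is a reporting floor that keeps the higher levels. The whole distribution is measured and averaged.
- The analysis section leaves the metric open and does not confine the search to 50%.
- The statement about 95% concerns skin in a fold. In the experimental arm "The IMF is effectively eliminated when using CARA". A fold is not required for entry, since lateral ptosis suffices, so the statement does not describe fold-free controls either. The 105% figure in Background refers to treated breast volume, not skin area.
- The measure is an area. It varies with fold size and surrounding dose even if all fold skin exceeds 50%. In the simulation it was weak, with an AUC of 0.56 to 0.64, but not empty.

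All four stand, and they reduce the dose-level limb to a request for clarity.

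On schedule, the fair reply is that silence is not a statement that schedules are pooled, that any percentage cut-off shares the problem, and that a journal article may leave exploratory detail to a fuller plan. The second part is right and only strengthens the case for handling schedule explicitly. On the others, the article does set out this comparison, by arm and by MD status at the film site, and it names fractionation as a covariate for the primary outcome. As written, the dose-area comparison has no such term, and it is the comparison that randomisation does not protect.

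Adding strata and dose levels to a limited film subset also thins the data and multiplies comparisons. That is a real cost and shapes the fix.

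**Conclusion.** The point holds in a limited form. As described, the within-arm comparison of dose-area data by MD status does not account for schedule. The article itself ties schedule to MD risk, and the one level it names spans 13 to 25 Gy (1.9-fold nominal; 1.7-fold in EQD2 with α/β = 10, 1.4-fold with α/β = 3, both values assumed). An association found or missed could therefore reflect schedule. The direction of any distortion cannot be determined from the document.

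Secondarily, if 50% were the sole cut-off it would probably discriminate poorly in control patients with a fold. This rests on the article's statement about fold dose and on an illustrative simulation. It does not extend to the CARA arm or to controls without a fold, and it falls away if 50% is only a floor.

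This is a cheap improvement to one secondary objective. The primary endpoint, the sample size and the randomised comparison of arms are unaffected.

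**What to change.** **Statistical methods – secondary outcomes.** Make the MD versus no-MD dose-area comparison with fractionation schedule as a stratum or covariate, grouped as 5, 15–16 and 25–28 fractions.

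**In-vivo skin dosimetry.** State whether 50% is a cut-off or a floor. From the averaged film distributions, report the area above several levels, including at least one near the prescribed dose (for example 50, 80, 90, 95 and 105%), with each level given in percent and in Gy. Name one high-dose level in advance as the main candidate and label the others exploratory, which limits the extra comparisons.

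**Cost.** No further film, visit or patient is needed, only more analysis of films already planned. The price is thinner data. Even if all 110 patients per arm had film, the expected MD rates give at most 110 × 0.50 = 55 control and 110 × 0.30 = 33 experimental cases, an average of about 18 and 11 per schedule group. The real film subset will be smaller. This favours one estimate per arm adjusted for or stratified by schedule over separate conclusions for each schedule. Accounting for schedule will not remove differences in separation within a schedule group, so the result should still be presented as exploratory.
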